#### Intervention B

The triage decision in the ED is based on an interdisciplinary biopsychosocial and functional risk assessment by the treating physician (for medical risk) and the ED nursing team (for biopsychosocial risk) (Figure 3). Hospitalization criteria in the control group include: 1. severe illness, high fever (≥39°C), costovertebral angle tenderness or flank pain; 2. inability to take oral medications or fluids; dehydration; 3. questionable patient compliance; 4. complications of pyelonephritis and 5. co-morbidities. In the ProADM group, the subjective admission criterion 1 (severe illness, high fever, costovertebral angle tenderness, severely impaired health) is omitted (simple UTI) or replaced by objective ProADM cutoffs for patients with febrile UTI/pyelonephritis. In patients with simple UTI, we do not expect the ProADM levels to provide sufficient prognostic information and therefore do not include ProADM in their admission criteria. A standardized score (the post-acute care discharge score, PACD) [45] is used to stratify all patients as low or high risk for subsequent rehabilitation and care. The final triage decision is a consensus by physicians, nurses and patient (or relatives). If a consensus cannot be reached, the patient’s preference has priority.

**Figure 3 F3:**
[figure not shown]
**Risk assessment on admission - site-of-care decisions (ProADM on admission).** ICU: intensive care unit; PACD: post-acute care discharge score; ProADM: proadrenomedullin; UTI: urinary tract infection.

The clinical risk assessment of both doctors and nurses is standardized using medical stability criteria [46] and biopsychosocial and functional scores (*Selbstpflegeindex* (SPI) self-care index [45,47]) and is used to assess the suitability of patients for discharge from the hospital (Figure 4). The care and risk assessment bundle is implemented in both groups using behavioral and communication strategies proven to be highly effective [48].

**Figure 4 F4:**
[figure not shown]
**Risk assessment during hospitalization - site-of-care decisions (ProADM on day 3).** ICU: intensive care unit; PACD: post-acute care discharge score; SPI: *Selbstpflegeindex* self-care deficit score; UTI: urinary tract infection.

Levels of ProADM are measured on admission and on day 3. ProADM cutoff tertiles derived from patients with LRTI will be used for severity assessment [41]: <0.75 nmol/l; 0.75 to 1.5 nmol/l; >1.5 nmol/l. Physicians receive detailed information on how to interpret ProADM cutoffs and about the results from previous trials when ProADM was used in patients with LRTI [12,29,31,34,35,49-51]. ProADM is measured in an ethylenediaminetetraacetic acid (EDTA) plasma by a sandwich immunoassay (MR-ProADM, BRAHMS AG, Hennigsdorf, Germany) with an analytical detection limit of 0.08 nmol/l and a functional assay sensitivity of 0.12 nmol/l. It is available within 1.5 h upon ordering (24 h a day, daily).

Reassessment of the possibility for discharge from the acute-care hospital is based upon reaching medical stability at any time plus appropriate ProADM levels with particular emphasis on assessment on day 3 (Figure 4). On day 3, the treating physicians receive recommendations regarding discharge according to the clinical stability algorithm. Guidelines are displayed on handouts given to the treating physicians. Algorithm compliance is controlled by the study team and reasons for non-compliance are documented.

Discharge planning based on the biopsychosocial risk at admission (PACD ≥ 8) is initiated immediately and any need for action discussed at each round.

Patients with low medical risk or medically stabilized but high biopsychosocial requirements can be triaged to nurse-led care. The nursing staff is in charge of further management with medical input only at further request or if there is a medical deterioration.

Medically stable patients not fulfilling medical criteria and biopsychosocial, functional and organizational overruling criteria (see section “Overruling criteria for antibiotic treatment and hospitalization”) are considered suitable for discharge to home. Patients meeting biopsychosocial or functional overruling criteria and organizational criteria (waiting for a transfer to the non-acute setting) are referred to non-acute medical care (nurse-led care, health resort, rehabilitation, transitional care or long-term care) (Figure 4).

### Overruling criteria for antibiotic treatment and hospitalization

Medical overruling criteria for prolonged antibiotic therapy

1. Admission to ICU

2. Life-threatening co-morbidity

3. Complications: abscess, papillary necrosis, emphysematous pyelonephritis, acute renal failure (GFR < 30 ml/min or creatinine increase ≥50% from baseline level)

Medical overruling criteria for hospitalization

1. Admission to ICU

2. Life-threatening co-morbidity

3. Complications: pyelonephritis, acute renal failure (GFR < 30 ml/min or creatinine increase ≥50% from baseline level)

4. Antibiotics or hospitalization (regardless of indication) within the last week

5. Confusion, delirium or intravenous drug abuse

Biopsychosocial and functional overruling criteria for hospitalization

1. Dementia, recurrent falls, pressure ulcer and inability to reliably take medications

2. SPI score <32 (during hospitalization)

3. Deficit of mobility

Organizational overruling criteria for hospitalization

1. Waiting for results that may alter the management, lab controls, investigations or therapy

2. Waiting for relocation to a non-acute medical care facility

3. Weekend or night

Preferences of the patient and the relatives

1. Patient and relatives concern about safety at home

2. Lack of nursing care

3. Financial reasons

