### Definitions

UTI is defined by at least one clinical symptom (core body temperature ≥38.0°C, urinary urgency, polyuria, dysuria, suprapubic pain, flank pain, costovertebral angle tenderness, nausea and vomiting) and one urinary criterion (pyuria >20 leukocytes/μl [39] and/or nitrites). A UTI is defined as febrile UTI/pyelonephritis if there is flank pain, costovertebral angle tenderness or a body temperature ≥38°C, and otherwise as simple UTI. A UTI is defined as complicated if any of the following criteria are fulfilled: male gender, age >70 years, symptoms >7 days, recent antibiotic therapy (within 30 days), recurrent UTIs (two or more during the last 6 months or three during the last 12 months), recent urologic intervention (30 days), functional or anatomic abnormality, diabetes mellitus or immunosuppressive therapy; otherwise UTI is considered uncomplicated for example, young non-pregnant women.

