#### Measurements

Urine sediment analysis, urine culture with an antibiotic resistance profile and urinary protein profile (α1-microglobulin/creatinine ratio) are performed on admission. In patients with a diagnosis of febrile UTI/pyelonephritis, blood cultures are taken prior to administration of antibiotics. These patients also receive an ultrasound evaluation of the urinary tract, including Doppler examination as well as a CEUS examination of both kidneys.

Chargeable and effective costs will be gathered from the finance and controlling departments to calculate costs per patient from study entry until discharge to a non-hospital setting. Data on outcome and complications will be collected by the study team.

All patients are called by members of the study team (who are unaware of the randomization group) on days 30 and 90 after randomization to inquire about clinical recurrences, antibiotic side effects and the preparedness for discharge [52] using a questionnaire with a ten-point Likert scale response format. Interviews are standardized according to a protocol and interviewers receive formal introductory training.

Physicians in this trial know that their behavior is monitored. Since it is not feasible to have ProADM and PCT values blinded in the control groups, however, algorithm compliance is reinforced according to assigned groups by the study team.

Both contrast-enhanced ultrasound criteria and urinary protein profiles are used together with urine and clinical criteria and biomarker levels for the final classification as upper or lower UTI. For final analysis, culture confirmation will be required (Table 1).

**Table 1 T1:** Urine culture cutoffs for significance

**Diagnosis**	**Criteria**
Uncomplicated, simple UTI	≥10^3^ cfu/ml
Uncomplicated febrile UTI/pyelonephritis	≥10^4^ cfu/ml
Complicated UTI (simple or febrile UTI/pyelonephritis)	
in women	≥10^5^ cfu/ml
in men	≥10^4^ cfu/ml
in straight catheter urine	≥10^4^ cfu/ml

cfu: colony-forming unit; UTI: urinary tract infection.

Healthcare-related quality of life on the day of discharge is measured with the EQ-5D questionnaire. EQ-5D includes the 15-item EQ-5D self-classifier, which assesses the health-related quality of life among five dimensions and the EQVas, which obtains a self-rating of the current health-related quality of life [53].

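### The hospitalization overruling list names pyelonephritis itself instead of its complications; read literally, this can set aside ProADM advice in the only group with ProADM admission cutoffs (minor)

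*Protocol article*

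**What the plan says.** Three places in the protocol article bear on when pyelonephritis justifies admission.

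- **Intervention B** lists five control-group admission criteria. The first is "1. severe illness, high fever (≥39°C), costovertebral angle tenderness or flank pain". The list ends with "4. complications of pyelonephritis and 5. co-morbidities". In the ProADM group only criterion 1 changes: it "is omitted (simple UTI) or replaced by objective ProADM cutoffs for patients with febrile UTI/pyelonephritis". ProADM is not an admission criterion in simple UTI.
- **Definitions** sets the group concerned: "A UTI is defined as febrile UTI/pyelonephritis if there is flank pain, costovertebral angle tenderness or a body temperature ≥38°C". All other UTIs are simple.
- **Overruling criteria for antibiotic treatment and hospitalization** has two medical lists. In the list for prolonged antibiotics, item 3 reads "3. Complications: abscess, papillary necrosis, emphysematous pyelonephritis, acute renal failure". In the list for hospitalization, item 3 reads "3. Complications: pyelonephritis, acute renal failure".

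The section on measurements adds that imaging, urinary protein profile, clinical criteria and biomarkers are used together "for the final classification as upper or lower UTI".

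**The concern.** The hospitalization list prints the diagnosis where the other two places name its complications. The location makes this more than cosmetic. ProADM can change an admission decision through its cutoffs only in febrile UTI/pyelonephritis, where it replaces a set of clinical signs. If pyelonephritis is itself an accepted reason to overrule, those signs can return as grounds for admission.

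The effect would fall mainly on one arm. In the control arm, flank pain, costovertebral angle tenderness and fever of 39°C or more are already admission criteria, so item 3 adds only fever of 38 to 38.9°C. In the ProADM arm it could bring back what was removed. Any use of the entry would therefore make the arms more alike on length of physician-led hospitalization.

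Two secondary analyses could be touched as well. Under Statistical considerations, the per-protocol population drops patients whose triage recommendation was overridden without a reason specified in advance. Secondary endpoint B of Intervention B hypothesizes adherence 20% higher in the intervention group. If pyelonephritis alone is accepted as a valid reason, an admission against low-ProADM advice could stay in the per-protocol set or be scored as adherent.

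**Working it through.** The point is textual. The only figure tied to this comparison is the Intervention B sample size, and it is sound: with a difference of 1.5 days, SD 4, two-sided 5% alpha and 80% power, n per arm = 2 × (1.960 + 0.842)² × 4² / 1.5² = 111.6, which rounds up to the stated 112. Nothing below alters it.

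**Step 1: compare the three wordings.** Intervention B, criterion 4: complications of pyelonephritis. Antibiotic list, item 3: three named complications plus acute renal failure. Hospitalization list, item 3: pyelonephritis plus acute renal failure. The third stands alone, and no other text in the article limits it.

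**Step 2: count what the literal reading brings back.** Criterion 1 as numbered has 4 elements: severe illness, fever of 39°C or more, costovertebral angle tenderness, flank pain. How many return depends on what pyelonephritis means in item 3.

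- Merged category from Definitions (flank pain, tenderness, or temperature of 38°C or more): every fever of 39°C or more also meets the 38°C limit, so 3 of 4 return, with the fever threshold 39 − 38 = 1°C lower.
- Flank pain or tenderness only, without fever: 2 of 4 return.
- Pyelonephritis as finally classified under Measurements: fewer patients would meet the entry, and the article gives no figure.

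These are counts of listed signs, not of patients.

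**Step 3: place item 3 among the other override routes.** Entries that can support hospitalization: 5 medical + 3 biopsychosocial and functional + 3 organizational + 3 preferences = 14. Correcting item 3 leaves 14 − 1 = 13 others untouched, including "3. Weekend or night".

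**Step 4: look for a size in days or power.** That would need the share of febrile UTI/pyelonephritis patients, the share of them with ProADM low enough to advise against admission, and how often physicians would invoke item 3. The article gives none of these, so any power figure would only restate an assumed dilution.

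**The case against.** The strongest reply is that this is a typing slip with no shown consequence. The section that sets the admission rule has the right wording, criterion 4 there is unchanged by randomization, and item 3 itself sits under the label of complications. Physicians work from the algorithms in Figures 3 and 4 and from handouts, none of which is shown. Final triage is by consensus, with patient preference deciding if there is none, and 13 other entries stay available. ProADM also acts on day 3 through discharge. Most of this stands and is why the point is minor. It does not remove the point: item 3 is a stated rule, it conflicts with another stated rule, and the text does not say which prevails.

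A second reply is that item 3 may mean a simple UTI that progresses to pyelonephritis. This is possible but strained, because under Definitions such a patient would then belong to febrile UTI/pyelonephritis, the group with the cutoffs.

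A reader might go further and infer three things that the article does not support.

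- *That ProADM advice can always be overruled in this group.* A patient with fever alone falls in the merged category but need not be called pyelonephritis, and Measurements allows a narrower classification. Patients whose ProADM favours admission are unaffected.
- *That the per-protocol set and the adherence endpoint are compromised.* The article does not say that this list supplies the reasons specified in advance, or that an item 3 admission counts as adherent. Leaving that detail to an analysis plan is normal and is not criticized here.
- *That the primary analysis loses power.* It follows intention to treat, so it is affected only if physicians actually use the entry.

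**Conclusion.** The conflict holds as a minor point. Item 3 of the hospitalization list contradicts the Intervention B criteria and the parallel antibiotic item. Taken literally, it lets the diagnosis justify admission against low-ProADM advice in the one group where the admission cutoffs apply, which would move the ProADM arm towards control. Its reach is 3 of 4 replaced elements on the merged definition and 2 of 4 without fever. The effect on length of stay cannot be quantified from the article.

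This rests on the text alone. The probable explanation is a drafting slip, and if the figures and handouts carry the correct wording, patient care may never have been affected. The 112 per arm and the primary analysis stand unchanged.

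**What to change.** Reword item 3 to *Complications of pyelonephritis (abscess, papillary necrosis, emphysematous pyelonephritis), acute renal failure*, keeping the present GFR and creatinine limits. Check that Figures 3 and 4 and the physician handouts agree. When adherence or per-protocol status is classified, do not accept pyelonephritis alone as a valid override.

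The cost is one phrase, plus the same phrase in the handouts if they share it. Intervention B already has the study team record why the algorithm was not followed, so patients already enrolled can be classified from those records, and no new data collection is expected.

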#### Measurements

Urine sediment analysis, urine culture with an antibiotic resistance profile and urinary protein profile (α1-microglobulin/creatinine ratio) are performed on admission. In patients with a diagnosis of febrile UTI/pyelonephritis, blood cultures are taken prior to administration of antibiotics. These patients also receive an ultrasound evaluation of the urinary tract, including Doppler examination as well as a CEUS examination of both kidneys.

Chargeable and effective costs will be gathered from the finance and controlling departments to calculate costs per patient from study entry until discharge to a non-hospital setting. Data on outcome and complications will be collected by the study team.

All patients are called by members of the study team (who are unaware of the randomization group) on days 30 and 90 after randomization to inquire about clinical recurrences, antibiotic side effects and the preparedness for discharge [52] using a questionnaire with a ten-point Likert scale response format. Interviews are standardized according to a protocol and interviewers receive formal introductory training.

Physicians in this trial know that their behavior is monitored. Since it is not feasible to have ProADM and PCT values blinded in the control groups, however, algorithm compliance is reinforced according to assigned groups by the study team.

Both contrast-enhanced ultrasound criteria and urinary protein profiles are used together with urine and clinical criteria and biomarker levels for the final classification as upper or lower UTI. For final analysis, culture confirmation will be required (Table 1).

**Table 1 T1:** Urine culture cutoffs for significance

**Diagnosis**	**Criteria**
Uncomplicated, simple UTI	≥10^3^ cfu/ml
Uncomplicated febrile UTI/pyelonephritis	≥10^4^ cfu/ml
Complicated UTI (simple or febrile UTI/pyelonephritis)	
in women	≥10^5^ cfu/ml
in men	≥10^4^ cfu/ml
in straight catheter urine	≥10^4^ cfu/ml

cfu: colony-forming unit; UTI: urinary tract infection.

Healthcare-related quality of life on the day of discharge is measured with the EQ-5D questionnaire. EQ-5D includes the 15-item EQ-5D self-classifier, which assesses the health-related quality of life among five dimensions and the EQVas, which obtains a self-rating of the current health-related quality of life [53].

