### Outcomes and adverse events

The primary endpoint for Intervention A is overall exposure to antibiotics in the PCT and pyuria guidance group compared to the control group. Endpoints are assessed at discharge from hospital, and 30 and 90 days after admission. As secondary endpoints, we will compare the PCT-pyuria group with the control group regarding:

A. Clinical and microbiological cure 7 days after end of therapy.

B. 30-day rate of clinical and microbiological recurrence.

C. 90-day rate of clinical and microbiological recurrence.

D. Antibiotic-associated side effects.

Regardless of group assignment, we will investigate:

E. The relationships of pyuria, urine culture cutoffs and urinary α1-microglobulin/creatinine ratio with the presence of pyelonephritis and level of biomarkers (CRP, PCT, ProADM, and other biomarkers such as urea, natriuretic peptides (ANP, BNP), copeptin, endothelin, apoprotein A1).

F. Correlation between sonographic signs of pyelonephritis and diagnosis based on urine culture cutoffs, clinical criteria and biomarkers.

Our hypothesis for the secondary endpoints A to C is that there is no difference between the two study groups. Our hypothesis for endpoints E and F is that urinary markers and contrast-enhanced ultrasound correlate with systemic biomarkers and diagnosis of pyelonephritis.

For the primary endpoint for Intervention B, we assess the length of physician-led hospitalization in the ProADM-guided triage group compared to the control group within a follow-up of 90 days. As secondary endpoints, we will compare the ProADM group with the control group regarding:

A. resource utilization, defined as the length of index hospitalization (physician- and/or nurse-led); rate and length of re-hospitalization; rate of general practitioner visits; rate of medical investigations and interventions related to UTI and overall, rate of treatment changes related to UTI, for example, antibiotic escalations. The hypothesis is that there are no excess re-hospitalizations or visits to the GP while there are fewer treatment changes and medical investigations in the ProADM group.

B. Proportion of patients triaged according to the risk assessment bundles. The hypothesis is that physician adherence to site-of-care decisions will be 20% higher in the intervention group.

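### Endpoint E's link between urinary markers and pyelonephritis is inflated if its reference is the final upper/lower UTI classification, which contains those markers; endpoint F can speak only about febrile UTI/pyelonephritis

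*Protocol article*

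**What the plan says.** In the protocol article, Measurements sets out how the final diagnosis is made: the contrast-enhanced ultrasound criteria and the urinary protein profile "are used together with urine and clinical criteria and biomarker levels for the final classification as upper or lower UTI". It identifies the protein profile and its timing: "urinary protein profile (α1-microglobulin/creatinine ratio) are performed on admission". Contrast-enhanced ultrasound is tied to patients with a diagnosis of febrile UTI/pyelonephritis: "These patients also receive an ultrasound evaluation of the urinary tract", including the contrast-enhanced examination of both kidneys.

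Outcomes and adverse events lists two endpoints for Intervention A that are studied regardless of group assignment. Endpoint E covers the relationships of pyuria, "urine culture cutoffs and urinary α1-microglobulin/creatinine ratio with the presence of pyelonephritis and level of biomarkers". Endpoint F is "Correlation between sonographic signs of pyelonephritis and diagnosis based on urine culture cutoffs, clinical criteria and biomarkers". The hypothesis for both is that "urinary markers and contrast-enhanced ultrasound correlate with systemic biomarkers and diagnosis of pyelonephritis".

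Definitions gives a separate, purely clinical definition: "A UTI is defined as febrile UTI/pyelonephritis if there is flank pain, costovertebral angle tenderness or a body temperature ≥38°C". All other UTIs count as simple.

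**The concern.** A diagnostic marker should be compared with a reference that does not contain it. If it is compared with a composite that it helped to form, part of the association exists by construction. This is incorporation bias, and here it favours what the investigators expect to find.

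The only diagnosis that the article calls final is such a composite. Background equates upper tract involvement with pyelonephritis, so a reader could well take the presence of pyelonephritis in endpoint E to mean upper UTI in that classification. A positive result for the α1-microglobulin/creatinine ratio or pyuria would then be hard to separate from the way the label was built.

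Endpoint F raises a different question. If ultrasound is done only in patients already diagnosed with febrile UTI/pyelonephritis, F says nothing about whether ultrasound tells these patients apart from those with simple UTI.

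**Working it through.** The article states no power, sample size or expected correlation for E and F, so there is no figure to reproduce. The check has two parts.

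**1. Each tested relation set against the classification**

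| Relation | Compared with | Tested marker in the final classification? | Circular? |
|---|---|---|---|
| E: α1-microglobulin/creatinine ratio | presence of pyelonephritis | yes, by name | yes if the final classification is the reference; no under the clinical definition |
| E: pyuria | presence of pyelonephritis | probably, as a urine criterion | same |
| E: urine culture cutoffs | presence of pyelonephritis | probably, as a urine criterion; the Table 1 cutoffs also differ by diagnosis | same, and in any reference that uses Table 1 |
| E: urinary markers | biomarker levels | classification not used | no |
| F: sonographic signs | diagnosis from culture cutoffs, clinical criteria and biomarkers | ultrasound is not in this comparator | no as worded; yes only if the final classification is substituted |
| Joint hypothesis: ultrasound | systemic biomarkers | classification not used | no |

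**2. How large the artefact could be**

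The article gives no rule or weights for the classification, so both calculations below rest on assumptions.

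*Two-of-three rule.* Assume three criteria with at least two needed, 40% prevalence, two criteria with 80% sensitivity and specificity, and a third that is pure noise, positive in 40%. All are independent given disease status.

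- Noise marker positive: at least one of the other two must be positive. P(upper) = 0.4 × (1 − 0.2²) + 0.6 × (1 − 0.8²) = 0.4 × 0.96 + 0.6 × 0.36 = 0.60.
- Noise marker negative: both others must be positive. P(upper) = 0.4 × 0.8² + 0.6 × 0.2² = 0.4 × 0.64 + 0.6 × 0.04 = 0.28.
- Overall P(upper) = 0.4 × 0.60 + 0.6 × 0.28 = 0.408.
- Apparent sensitivity = 0.24 / 0.408 = 0.588.
- Apparent specificity = (0.6 × 0.72) / 0.592 = 0.432 / 0.592 = 0.730.
- Apparent odds ratio = (0.60/0.40) / (0.28/0.72) = 3.86. The true value is 1.

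*Weighted score.* Let the classification be a cut at zero of a normal score in which the tested marker, unrelated to every other component, carries a share s of the variance. Then r = √(2s/π). The chance of a significant result (two-sided 0.05) is about Φ(atanh(r)·√(n−3) − 1.96). The planned n is 250; after the anticipated 20% loss it is 250 × 0.8 = 200.

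| Share s | r | n = 200 | n = 250 |
|---|---|---|---|
| 5% | 0.18 | 72% | 81% |
| 10% | 0.25 | 95% | 98% |
| 20% (five equal components) | 0.36 | about 100% | about 100% |
| 33% (three equal components) | 0.46 | about 100% | about 100% |

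A simulation with 1,000,000 draws gave the same r values. With three to five equal components the area under the ROC curve was 0.77 to 0.71. With the tested marker left out of the classification, r was 0.00 and the area 0.50. Required culture confirmation would make n smaller than shown, which lowers the chance of significance but not r.

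**The case against.** A reader might infer that E and F are both circular throughout and that ultrasound, urinary protein and systemic biomarkers are all tested against a label containing them. The documents do not support that.

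- F's own definition names a diagnosis without ultrasound, so it already does what good practice asks. Only the looser joint hypothesis, which speaks of the diagnosis of pyelonephritis without saying which, leaves room for the composite.
- Systemic biomarkers are not tested against the classification. In E they are a second variable set directly against the urinary markers; in F they belong to the comparator.
- For E, the clinical definition is available and contains none of the tested markers. The article does not say that the composite is the reference, and the full protocol may settle it.
- The two-of-three illustration is harsher than five kinds of input would suggest: r falls from 0.46 with three equal components to 0.36 with five.
- E and F are secondary and worded as relationships and correlations.

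All of this stands, and it narrows the point. It does not remove it. The article states a composite built from the tested markers, calls it final, and offers more than one candidate for the reference in E. Adding components weakens the artefact, but at a 5% share an unrelated marker would still reach significance about 81% of the time at n = 250.

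**Conclusion.** The point holds conditionally for E. If the final upper/lower classification serves as the reference, the associations of the α1-microglobulin/creatinine ratio and, probably, pyuria with pyelonephritis are inflated in the direction of the hypothesis. The direction is certain under that reading. The size is not, because the classification rule is not given; the illustrations run from r = 0.18 to 0.46, or an odds ratio of 3.9, for a marker with no value at all. Under the clinical definition this problem does not arise.

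F is not circular as worded and would become so only if the composite replaced its stated comparator. It would be wrong to conclude that no positive result from E or F could be interpreted, since the direct correlations with systemic biomarkers do not use the classification.

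The limit on F holds under either reading. Taking the diagnosis in Measurements to be the one in Definitions, no patient with simple UTI is planned to have contrast-enhanced ultrasound, so F cannot show discrimination from simple UTI.

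The change is worth making before analysis. It touches neither the antibiotic exposure comparison nor the length-of-stay comparison.

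**What to change.** For the pyelonephritis part of E, name the reference. Either use the clinical-only definition in Definitions, which separates febrile from simple UTI without urinary protein, pyuria, culture cutoff or biomarker, or rebuild the composite without the marker under test, separately for each marker and assigned without knowledge of it. When culture cutoffs are the tested variable, keep the Table 1 cutoffs out of the reference.

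For F, keep the ultrasound-free comparator as worded. Do not replace it with the composite, which would bring ultrasound into the reference, or with the clinical definition, which every scanned patient meets and which would leave nothing to correlate. State that F's conclusions apply only within clinically febrile UTI/pyelonephritis. Align the joint hypothesis with these references, and keep the composite for description.

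Cost: if the clinical definition is used, wording only. A rebuilt composite also means reclassifying patients once per tested marker, from data already collected. The reported associations will probably be weaker, and the clinical definition is a less refined reference than the composite.
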